**Fig. 1 Fig1:**
[figure not shown]
The OPTION project work packages: overall focus, and timeline (WP, work package)

The specific aims of each work package of the project are as follows:
To investigate the incidence of urinary retention, bladder distension and complications among hip surgery patients; the procedures to prevent, detect, and manager urinary retention performed by staff; the hip surgery patients’ experience of voiding issues during the orthopaedic care episode, including the conditions for participation in such issues; staff and managers’ experience of guideline implementation in general and in urinary retention in particular; and staff experience of contextual factors known to influence knowledge implementation (WP1).To provide an implementation support programme for the local facilitator teams, including managers, for 12 months to the sites randomised to the intervention (WP2).To explore the outcomes in terms of attitudes and behaviours in terms of urinary retention and voiding care among staff and managers post intervention, including the procedures to prevent, detect, and manager urinary retention performed by staff, comparing the intervention sites with the control sites (WP3).To explore the outcomes in terms of the incidence of urinary retention, bladder distension and complications among hip surgery patients during and after the hospital care episode, and the hip surgery patients’ experience of voiding issues during and after the orthopaedic care episode, including the conditions for participation in such issues (WP4).To evaluate the activities of the support programme in relation to the contextual factors of the orthopaedic sites, and the activities and actors performed across intervention and control sites, respectively, identifying what influenced the process of facilitation implementation and de-implementation of evidence-based urinary retention care. This includes considering contextual factors, such as barriers and enablers for knowledge translation, and the cost associated with adhering to or diverging from guidelines (WP5).

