### Power and sample

The study power calculation is based on opportunities to detect an impending increase in adherence to national bladder monitoring guidelines: assuming an absolute increased adherence to the guidelines of 15% (50% in the control group and 65% in the intervention), the required sample size is 227 patients in each arm, with 90% power and two-sided significance level of 0.05 (based on an intracluster correlation coefficient of 0.03). With 10 clusters in each arm and an average cluster size of 70 patients, a total of 1380 patients are needed. Considering a dropout rate of 10%, a total sample size of 1500 is required, providing an average cluster size of 75 patients. With a variance between around 5% and 80% incidence of urinary retention among hip surgery patients, it is difficult to calculate power based on this factor. Yet, considering that it may be 35–40%, the cluster size suggested above will also allow detecting a 15% absolute difference in incidence of urinary retention between the intervention group and the control group post intervention.

Once the units had agreed and the ethics board had approved the trial, the randomisation was performed. To prevent bias in terms of complexity of the patients’ medical status, and influence of clinical training programmes for students in nursing science and physio- and occupational therapy, university hospitals were equally distributed as intervention and control units. Further, two units located in Stockholm, the capital of Sweden, were randomised to either intervention or control. Thus, the randomisation was completed in four steps: university units, units in the Stockholm catchment area, and regional orthopaedic and local orthopaedic units, respectively, drawn from sealed envelopes by an impartial researcher engaged for this procedure whilst monitored over video link by the research team.

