### Data collection

The primary outcome measure for OPTION is:
Adherence to urinary retention guidelines in the care of patients undergoing hip surgery.

Additional outcomes are:
A.Incidence of and severity of urinary retention, bladder distension, and voiding complications among hip surgery patients (WP1, WP4 and WP5).B.Activities and experiences of urinary retention, bladder distension, and voiding complications care among nursing and rehabilitation staff in orthopaedic care (WP1, WP3, and WP5).C.The IFs’ and managers’ experiences of the facilitation programme (WP2 and WP5).D.The patients’ experience of bladder care and voiding self-care management during the hospital stay and post discharge, including conditions for participating in these health-related issues (WP1, WP4, and WP5).E.Use and costs of urinary retention devices and labour related to bladder monitoring (WP5).

Hence, data will be collected as follows:

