A.Quantitative data regarding urinary retention will be collected from patient records, including bladder monitoring, voiding and healthcare interventions, by means of a structured template [12, 22] at baseline, post completion of the study intervention, and an additional, 1-year follow-up.B.Structured patient record assessment in triangulation with qualitative interviews with a random sample of nursing and rehabilitation staff and managers across all sites [13, 23, 25, 38]. In addition, baseline data collection includes mapping the context, with the Alberta Context Tool (ACT) [39, 40] distributed among all nursing and rehabilitation staff.C.Qualitative interviews post intervention (follow-ups I and II), in addition to voice recordings of all events during the intervention (support programme) [13, 23, 41]. Further, IF teams and managers will be asked to keep notes, by means of an individual, semi-structured reflective diary [42].D.Structured patient record assessment in triangulation with a post-discharge structured survey to all hip surgery patients for voiding difficulties after the hospital episode, self-care management and conditions for participating in accordance with one’s preferences—the latter using the 4Ps tool (Patient Preferences for Patient Participation) [43–45]. Further, data will originate from qualitative interviews with a sample of two patients per data collection point and site, representing the age range and gender distribution among those having had hip surgery.E.The structured patient record assessments at baseline, follow-up I and follow-up II will inform the health economics evaluation.

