### Data analysis

Data from patients’ records, the Alberta Context Tool questionnaire, the patient survey on voiding difficulties, and patient participation will be analysed with statistical analyses [46]. Between-group differences will be analysed using Student’s independent-sample t test for continuous variables, the Mann–Whitney U test for non-normally distributed continuous variables, and a χ2 test for nominal variables.

Qualitative content analysis will be applied for all interviews [47, 48], subsequently transcribed verbatim to text files by a professional service.

All data will be considered in the final mixed methods [49], embedding the process evaluation [50].

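### The normality-based test rule makes no exception for resource use and costs; if these are skewed it selects Mann–Whitney, which does not compare mean cost

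*Protocol article*

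**What the plan says.** All references are to the Methods of the protocol article.

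- **Data collection, additional outcomes.** Outcome E, the last of five additional outcomes, is "Use and costs of urinary retention devices and labour related to bladder monitoring (WP5". The primary outcome is guideline adherence.
- **Data collection, sources (item E).** "The structured patient record assessments at baseline, follow-up I and follow-up II will inform the health economics evaluation".
- **Aims, WP5.** The evaluation includes "the cost associated with adhering to or diverging from guidelines (WP5".
- **Data analysis.** The scope sentence reads "Data from patients’ records, the Alberta Context Tool questionnaire, the patient survey on voiding difficulties, and patient participation will be analysed with statistical analyses". Between-group differences then follow one rule: Student's t test for continuous variables, "the Mann–Whitney U test for non-normally distributed continuous variables", and a chi-squared test for nominal variables.

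No section exempts costs from this rule, and none gives another method for them. No section gives a cost figure, a standard deviation or a distribution.

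**The concern.** The rule chooses the test by the shape of the data and not by the question. Per-patient use and cost of bladder care will probably be right-skewed: many patients have a few inexpensive checks, and a minority have an expensive episode. The rule would then lead to Mann–Whitney.

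Mann–Whitney asks whether a random patient in one arm tends to rank above a random patient in the other. A cost comparison that is to scale up to a total bill needs the difference in arithmetic means. The two can diverge when the distributions cross. The hypothesis in the Aims section points to such a pattern: more prevention and detection for patients in general, and less bladder distension with fewer later symptoms. Ranks register a small rise in cost for most patients but give little weight to the size of a large saving in a few.

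At stake is a statement that bladder care in the intervention arm costs significantly more when its mean cost is the same or lower.

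**Working it through.** **1. The plan's own figures, used only to set the simulation sizes.** The plan assumes adherence of "50% in the control group and 65% in the intervention" and states that "the required sample size is 227 patients in each arm, with 90% power and two-sided significance level of 0.05". The ICC that it uses is 0.03.
- The pooled two-proportion formula for 50% v 65%, 90% power and two-sided 5% gives 227 per arm, as stated.
- With 69 patients per site, the design effect is 1 + (69 − 1) × 0.03 = 3.04.
- The total is 2 × 227 × 3.04 = 1380, as stated, or 690 per arm.

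The simulations therefore use 690 per arm (the actual number) and 225 or 227 per arm (about the effective number, 690 / 3.04 = 227). Patients are simulated as independent, to keep this issue apart from clustering.

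**2. First cost model. All cost inputs are assumptions.** Cost = Poisson number of monitoring events × 1 unit + (episode yes/no) × gamma cost with mean 20 units and coefficient of variation 1. Control arm: 2 events and 20% episodes, so mean = 2 + 0.20 × 20 = 6. Two-sided 5% tests, 2000 simulated trials per row.

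| Intervention arm | Mean cost | Mann–Whitney rejects, 690 / 225 per arm | Welch t rejects, 690 / 225 |
|---|---|---|---|
| 2.25 events, 18.75% | 2.25 + 3.75 = 6 | 42% / 17% | 5% / 5% |
| 2.5 events, 17.5% | 2.5 + 3.5 = 6 | 92% / 49% | 5% / 4% |
| 3 events, 15% | 3 + 3 = 6 | 100% / 96% | 5% / 5% |
| 3 events, 10% | 3 + 2 = 5 | over 99% / 86%, as dearer | 44% / 16% |
| 2 events, 20% (identical arms) | 6 | 5% / 5% | 6% / 5% |

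A separate rerun gave 93% / 48% for the second row and 99.8% / 87% for the fourth, all in the dearer direction. In the fourth row, where mean cost falls, Welch's test did not point to dearer at 690 per arm. With identical arms both tests hold about 5%, so what differs is the hypothesis tested, not the error control.

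**3. Second cost model, also assumed.** Lognormal routine cost (mean 100 in control) plus a lognormal episode cost (mean 1000) in 20% of control patients, so mean = 100 + 0.20 × 1000 = 300. 1000 simulated trials per row.

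| Intervention arm | Mean cost | Mann–Whitney 'dearer', 690 / 227 per arm | Student t 'dearer', 690 per arm |
|---|---|---|---|
| 120, 18% | 120 + 180 = 300 | 95% / 58% | 2% |
| 120, 15% | 120 + 150 = 270 | 84% / 39% | 0% |
| 120, 10% | 120 + 100 = 220 | 37% / 15% | 0% |
| 150, 10% | 150 + 100 = 250 | 100% / 98% | 0% |

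**4. Where the reversal does not occur.**
- All costs multiplied by 0.85 (a single lognormal): at 690 per arm Mann–Whitney says cheaper in 83% and dearer in 0%.
- Monitoring unchanged and only episodes fewer: no reversal. Costs in the intervention arm are then shifted downwards throughout, so ranks and means move the same way.

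The reversal therefore needs a crossing pattern: higher routine cost for most patients together with fewer costly episodes.

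**The case against.** **The link from the test rule to costs is inferred.** The scope sentence in Data analysis does not name costs. The records are only said to inform a health economics evaluation, and the article does not describe its method. A derived cost also needs unit prices and labour valuation, and such methods are commonly left to a fuller plan. This stands in part. A reader might infer that the plan commits its economic evaluation to Mann–Whitney; the documents do not say that. They do state one rule for patient-record data, take outcome E from those records, and make no exception. The point is about that stated rule.

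**A reader might infer that the trial could report the support programme as dearer.** The documents do not support this. Outcome E covers devices and monitoring labour; the cost of the 12-month support programme is not in patient records. At most, the cost of bladder care in the intervention arm could be mislabelled.

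**The mean difference between arms is not stated as the target.** This is correct. The WP5 wording can be read as adherent against non-adherent care, and outcome E names no contrast. Mean cost is preferred here because it scales to a total.

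**The sizes are assumed.** This stands. Skewness, cost ratios and shifts are all chosen, no normality criterion is given, and the rule also allows a t test. The crossing pattern fits the trial's hypothesis, but nothing documents its size.

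**It would be too strong to say that the plan precludes a mean difference with an interval.** The section names tests only; it neither prescribes nor forbids estimates.

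**Conclusion.** The point holds in a limited form. Read literally, the rule sends skewed per-patient use or cost to a rank test, and the mechanism by which ranks and means can disagree is confirmed under two different cost models. At equal mean cost, with 2 to 2.5 events and 20% to 17.5% episodes, the false 'dearer' result occurs in about 48% (225 per arm) to 93% (690 per arm) of trials. Across the weaker and stronger equal-mean shifts in the first model, Mann–Whitney rejects in 17% to 100%.

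These figures rest on assumed costs, assumed skewness, independent patients and an assumed crossing pattern. They show what the rule can do, not what it will do in this trial. The primary outcome is unaffected, and outcome E is the last of five additional outcomes. The change is an optional improvement that the trial team could make, not a condition for a sound trial.

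**What to change.** Add to Data analysis that the t test/Mann–Whitney rule does not apply to outcome E. Suggested wording: *Resource use and costs will be compared between arms as the difference in arithmetic mean per patient with a 95% confidence interval, from a site-level analysis or a bootstrap that resamples sites within arm. Medians and quartiles will be given as description.* If a separate health economics plan already governs costs, one clause saying so would settle the point.

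A plain t test would not be enough, because it ignores clustering. If the ICC of 0.03 also applied to costs, then with 70 patients per site the design effect is 1 + 69 × 0.03 = 3.07, and a nominal 5% test has a true error of 2 × [1 − Φ(1.96 / √3.07)] ≈ 26%.

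The cost is a sentence or two of text and a little programming, with no new data or patients. The downside is a wider interval, because mean cost is sensitive to a few expensive patients.

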## Discussion

The OPTION project addresses elements of necessity to progress implementation science and clinical practice: team strategies for guideline implementation, including the managers’ role and function in relation to IFs, and barriers and enablers for safe bladder management in the orthopaedic care context. As such, it requires vigilant data collection and analysis [51], considering the theoretical and practical aspects of epistemology and methodology. Whilst we draw on previous studies, we expect the OPTION study to advance research issues by considering the effects of the implementation strategy for both patients and professionals [42].

For patients, increased adherence to guidelines for voiding care in the orthopaedic context can decrease the risk of adverse events and complications associated with hip surgery [52], particularly the often preventable risk of urinary retention [53]. Further, advanced interprofessional teamwork to address urinary retention is likely to incorporate the patient perspective, enhancing opportunities for individuals to participate in issues regarding their health and healthcare [43]. Whilst clinical measures are needed to determine the impact of the OPTION implementation strategy, the evaluation will augment the understanding of patient-related outcome measures in implementation science. In addition, healthcare professionals will have an option to progress from knowing what to do—learning about the readily available national guidelines—to providing orthopaedic nursing and rehabilitation care according to evidence-based standards. Any such change signifies altered clinical routines and modified attitudes and behaviours [25] addressed by the implementation strategy. If facilitating adoption of guidelines, the experiences of OPTION can be applied for knowledge translation in orthopaedic care and other surgical settings, across and beyond the participating hospitals and Swedish healthcare [54]. In the OPTION trial, details needed for a transparent trajectory in terms of the implementation process and outcomes are considered, particularly how the relations between the evidence, the facilitation, and the context can explain the outcomes [55]. For now, the lack of evidence-based procedures and the use of dated knowledge in health care cause substantial suffering for individual patients, at far too high a proportion of healthcare budgets.

## Data Availability

The data collection tools developed for the OPTION trial are available upon reasonable request from author [name], except for the 4Ps tool, which is available from author [name]. The Alberta Context Tool is used by courtesy of Professor [name], University of Alberta, Canada.
